### **34 Accountability**

Strict vaccine accountability procedure will be maintained. The accountability process will ensure that vaccines given to each subject are traceable for monitoring purposes.

It is NOT permitted to use any of the supplies provided by SIIL for purposes other than those specified in this protocol (i.e. vaccinating participants enrolled in the study and *in vitro* assays). Once final accountability is completed, unused supplies will be destroyed at site. If required, destruction at the site will be carried out according to local biosafety standards for disposal of biological waste material after written approval from SIIL has been received.

### **35 Presentation, packaging and labelling**

Study vaccine and diluent vials, along with the other vaccine supplies listed below, will be supplied by the manufacturer. For each participant, one carton will be provided containing the following:

1. Live attenuated influenza vaccine (single dose vial)
2. Diluent (0.5 ml) (single dose package)
3. Draw up needle
4. 1-ml Luerlock syringe
5. Intranasal spray device
6. Dose divider

### **36 Product storage and stability**

All lyophilized study vaccines must be stored in a safe, locked, and secure place with no access by unauthorized personnel. Vaccines must be kept in the refrigerator (+2°C to +8°C) and must not be frozen. Study vaccine is packaged as a single-dose preparation, and is intended to be administered immediately following reconstitution. However, should the vaccine be reconstituted and not used immediately, it must be stored at +2°C to +8°C for no more than 6 hours after reconstitution after which it must be discarded.

Storage temperature should be monitored daily. Access to a backup refrigerator in case of power failure/breakdown is necessary. Vaccines that have been stored differently from the recommendations must not be used unless the sponsor provides written authorization for use. The lyophilized vaccine formulation is highly stable if stored according to manufacturer recommendations; however, the expiration date printed on the outer box must not be exceeded.

### **37 Dosage, preparation and administration**

#### **38 Dosage**

A dose of 0.5 ml is administered as 0.25 ml per nostril using a syringe and a spray device while the subject is in an upright position with head tilted back slightly.

#### **39 Preparation**

Each vial of lyophilized vaccine must be reconstituted using 0.5 ml of sterile water that is supplied along with the vaccine.

#### **40 Administration**

The investigator, or designee, will be responsible for the preparation and administration of study vaccines to study participants according to the procedures in the study protocol and/or Study Specific Procedures (SSPs). All vaccines will be administered only by a study clinician or nurse who is qualified and trained to perform this function.

## 41 Contraindications and precautions

Nasovac-S is contraindicated in individuals with a history of hypersensitivity to eggs, egg proteins, gelatin, lactalbumin or other vaccine components listed in Table 5. Nasovac-S is also contraindicated in children receiving aspirin therapy, because of the association of Reye's syndrome with aspirin and wild-type influenza infection.

## 42 Safety data

Following a phase I of  $n = 40$  adults which showed no safety concerns, in 2012, SIIL began a Phase II/III human trial of Nasovac-S. This study was conducted among 330 healthy children (aged 2 through 17 years,  $n=110$ ), adults ( $n=110$ ), and the elderly ( $n=110$ ). Study vaccines included standard concentration LAIV (Formulation A) and a diluted LAIV comparator (Formulation B). In addition, the vaccine safety profile was favorable at both concentrations. There was no new onset of chronic medical conditions or SAEs identified among study participants, solicited adverse events were balanced between the groups, and 9 and 4 subjects in Formulations A and B respectively reported unsolicited AEs (SIIL Clinical Study Report, A Phase II/III clinical trial to assess safety and immune response of Trivalent, Live Attenuated Seasonal Influenza Vaccine of SIIL, 8 August 2012).

Out of 110 Pediatric subjects ( $\geq 2$  years and  $<18$  years) enrolled in the study, 46 children were  $\leq 5$  years, out of whom 24 received Formulation A (Group I) while 22 received Formulation B (Group II) (Table 5). Two children reported solicited local reactions. One child in Group I reported runny nose while another child from Group II reported stuffy nose. Both these events were of Grade I severity (mild), resolved without any sequelae within 2 days and didn't require concomitant medications. One child from Group II reported a solicited systemic reaction, cough, of Grade I severity (mild). It resolved without any sequelae, within one day and didn't require any concomitant medications. A total of ten unsolicited adverse events were reported from eight children. Unsolicited adverse events reported by children included abrasion on right forearm, abscess over left forearm, chickenpox, clean lacerated wound over chin, coryza, dog bite on right thumb, fever, loose motions and pain in abdomen. These were all judged to be unrelated to the vaccine. All of the unsolicited AEs resolved without sequelae within 1-9 days without need of concomitant medications. All except one of the AEs were Grade 1 (mild) in severity and no AE was reported as Grade 3 (severe). No death or SAE was reported in the study. None of the subjects experienced any hypersensitivity reaction. The safety data collected to date demonstrates that a single dose of both formulations of SIIL vaccine are safe and tolerable.

In June 2012, a Phase II safety and immunogenicity study was commenced in Bangladesh using Nasovac-S and the safety data are now published [31]. Of the 300 children included in the study and evaluated for safety and reactogenicity for the 42 day post-vaccination period, there were two unrelated SAEs (one fracture and one paracetamol overdose). There were no severe or life-threatening events. During the 7-day post-vaccination period, there were seven moderate solicited events and 102 mild solicited events (Table 5). During this same period there were 31 unsolicited events, of which 2 were moderate severity and the rest were mild (Table 6 shows unsolicited events across entire study). Episodes of protocol-defined wheezing (solicited) were not statistically different between LAIV and placebo groups during the 42-day period ( $n = 13$  and  $n = 16$  respectively,  $p = 0.697$ ). These were all of mild severity. 15 of these events had positive laboratory tests for respiratory viruses at the time (five adenovirus, seven respiratory syncytial virus, three human metapneumovirus). All of these events resolved without sequelae.

**Table 5. Solicited adverse event by vaccine group in first 7 days post-vaccination with Nasovac-S in Phase II safety and immunogenicity study in Bangladesh [31].**

| Solicited adverse event  | LAIV group
(n = 150) n (%) | Placebo group
(n = 150) n (%) | p-value |
|---------------------------------|---------------------------------------|------------------------------------------|----------------|
| Fever (measured 38C or higher)  | 5 (3.3)                               | 5 (3.3)                                  | 1.00           |
| Ear pain                        | 2 (1.3)                               | 2 (1.3)                                  | 1.00           |
| Cough                           | 10 (6.7)                              | 8 (5.3)                                  | 0.81           |
| Runny nose/nasal congestion     | 31 (20.7)                             | 34 (22.7)                                | 0.78           |
| Sore throat                     | 2 (1.3)                               | 0 (0.0)                                  | 0.50           |
| Headache                        | 1 (0.7)                               | 0 (0.0)                                  | 1.00           |
| Irritability/decreased activity | 0 (0.0)                               | 0 (0.0)                                  | -              |
| Vomiting                        | 2 (1.3)                               | 3 (2.0)                                  | 1.00           |
| Lethargy                        | 0 (0.0)                               | 0 (0.0)                                  | -              |

All events were mild except for moderate events fever (2 LAIV vs. 1. placebo) and cough (3 LAIV vs. 1 placebo). There were no severe events.

**Table 6. Participants with unsolicited adverse event by vaccine group over entire study period in Phase II safety and immunogenicity study of Nasovac-S in Bangladesh [31].**

| Adverse event classification    | LAIV group
(n = 150) n (%) | Placebo group
(n = 150) n (%) | p-value |
|----------------------------------------|---------------------------------------|------------------------------------------|----------------|
| Diarrhoeal illness                     | 38 (25.3)                             | 32 (21.3)                                | 0.50           |
| Oral thrush                            | 26 (17.3)                             | 18 (12.0)                                | 0.25           |
| Boil/abscess/skin infection/ulcer/cyst | 11 (7.3)                              | 18 (12.0)                                | 0.24           |
| Helminthiasis                          | 9 (6.0)                               | 11 (7.3)                                 | 0.82           |
| Scabies                                | 8 (5.3)                               | 6 (4.0)                                  | 0.79           |
| Abdominal pain/distension              | 5 (3.3)                               | 6 (4.0)                                  | 1.00           |
| Allergy                                | 6 (4.0)                               | 6 (4.0)                                  | 1.00           |
| Fungal infection                       | 6 (4.0)                               | 5 (3.3)                                  | 1.00           |
| Others                                 | 55 (36.7)                             | 51 (34.0)                                | 0.72           |

A safety and efficacy study of Nasovac-S was recently completed in the Niakhar region, Senegal, recruiting children aged 24 – 71 months in a randomized, double-blind, placebo-controlled design ([name], XVII International Symposium on Respiratory Viral Infections, Vancouver, CA, 2015). N = 1174 Nasovac-S vaccinated and n = 587 placebo-vaccinated (2:1) children were included. Local reactogenicity (cough, sore throat, runny nose, nasal congestion, ear pain) up to day 7 following vaccination was similar between the groups: with 20.6% and 19.9% of the LAIV and placebo group reporting mild symptoms, 0.4% and 0.2% reporting moderate symptoms and no subjects reporting severe symptoms. Systemic reactogenicity (chills, headache, vomiting, irritability/decreased activity, muscle/joint pain, documented fever, tachypnea) in the same timeframe was rare with 2.7% and 3.2% reporting mild symptoms in LAIV and placebo groups, 0.4% and 0.7% reporting moderate symptoms and 0.1% and 0.0% reporting severe symptoms respectively.

Of the unsolicited adverse events documented as occurring at greater than 1% frequency, 2.3% reported gastrointestinal disturbance (diarrhea, abdominal pain, vomiting, gastroenteritis, enteritis), with these equally balanced between the two groups and no severe symptoms noted. 1.9% were noted to have respiratory, thoracic or mediastinal events (bronchiolitis, nasopharyngitis, oropharyngeal pain, pneumonia, pulmonary congestion, runny nose), with more in the placebo arm (2.7%) than LAIV (1.4%). No life threatening events were noted. Protocol defined wheezing occurred in only one subject (0.2%) in the placebo arm at day 0 – 42 following vaccination and in four children in both the LAIV (0.3%) and placebo (0.7%) groups between day 43 to six months following vaccination.

These data combined provide robust safety data on Nasovac-S in children aged 2 years and over.

#### **43 Azithromycin**

Azithromycin is a macrolide antibiotic widely used in the treatment of community acquired infections in children and adults due to organisms such as *Haemophilus influenzae*, *Moraxella Catarrhalis*, *Streptococcus pneumoniae*, *Streptococcus pyogenes*, *Chlamydophila pneumoniae* and *Mycoplasma pneumoniae*. It has US FDA approval to treat acute otitis media in children ≥6 months, pharyngitis/tonsillitis in children ≥2 years and community acquired pneumonia in children ≥6 months.

Single-dose azithromycin has also been widely used in mass trachoma eradication campaigns, including those in The Gambia.

#### **44 Manufacturer**

Azithromycin (Zithromax®) for oral solution is produced by Pfizer corporation.

#### **45 Composition**

Zithromax® for oral suspension is supplied in bottles containing azithromycin dehydrate powder equivalent to 300mg, 600mg, 900mg, or 1200mg per bottle and the following inactive ingredients: sucrose; tribasic anhydrous sodium phosphate; hydroxypropyl cellulose; xanthan gum; FD&C Red #40; and flavoring including spray dried artificial cherry, crème de vanilla, and banana. After constitution, a 5mL suspension contains 100mg or 200mg of azithromycin.

#### **46 Acquisition, transportation and accountability**

Zithromax® will be procured via MRC pharmacy procurement procedures for medications from Pfizer corporation or authorized distributors and shipped according to manufacturer's

recommendations for clinical use. Once final accountability is completed, unused supplies will be donated to the MRC Unit The Gambia Clinical Services.

#### **47 Product storage and stability**

Zithromax® dry power is stable at temperatures below 30°C. As room temperature in The Gambia can exceed this, Zithromax® dry powder will be stored refrigerated at 2 - 8°C in MRC pharmacy stores prior to use. Reconstituted suspension is stable below 30°C for 10 days. Reconstituted suspension will also be stored refrigerated at 2 - 8°C in MRC biobank and transported to and from the field site in a cool box prior to use. A date of reconstitution and date of expiry (i.e. 10 days from reconstitution) will be noted on the bottle and those that are not used the date of expiry will be discarded.

#### **48 Dosage and administration**

Azithromycin will be administered as a single dose, in oral suspension form for children. Dosing will follow the WHO recommendations for treatment of active trachoma, which is a single dose of 20mg/kg in children (up to the maximum adult dose of 1g).

#### **49 Adverse reactions and precautions**

Azithromycin is well tolerated, particularly in the single dose regimens recommended for mass trachoma eradication campaigns by the WHO [68]. The most common side effects of azithromycin are diarrhoea, nausea, abdominal pain and vomiting, each of which may occur in fewer than one in twenty persons who receive single dose azithromycin. These are typically short-lived, lasting less than 24 hours [68]. Allergic reactions are rare.

### **50 Selection and withdrawal of participants**

#### **51 Selection of participants**

The study will randomize 330 children between 24 and 59 months, followed by sequential recruitment of a further 35 children within the same age range (see section 3.1), which allows for approximately 10% participant attrition during the study and required sample sizes to achieve primary objectives (Section 8). Screening of potentially eligible children will continue until this number or the recruitment end date (30.06.2018) is reached. Recruitment will take place over two six month periods, January – June 2017 and January – June 2018 (first subject first visit, FSFV to last subject first visit, LSFV of each season). These months have been chosen to coincide with periods when wild-type influenza infections are likely to be at their lowest, therefore least likelihood of interference with study endpoints. The recruitment target for season 1 (January – June 2017) will be 195 children (65:65:65 into groups A, B and C) and season 2 (January – June 2018) 170 children (45:45:45 into groups A, B and C, followed by 35 into group D – see section 3.1). This represents 29 – 33 children per month or approximately 7 - 8 children per week. Any shortfall in numbers caused by lack of recruitment or withdrawal in season 1 will be made up in season 2 by increasing target numbers.

#### **52 Identification of potential study subjects**

Healthy 24 – 59 month old children will be recruited via two main strategies: community sensitization will take place and parents encouraged to attend with their children to the Health Centre, where recruitment will take place. Older siblings of children attending the Health Centre for their expanded programme of immunization (EPI) schedule will also be recruited. Clinical trial staff stationed in this clinic will identify potential subjects in conjunction with the public health officers coordinating the clinic.

The parent/guardian will be approached by clinical trial staff to provide information and discuss participation. Under these circumstances, an opportunity will always be offered for a parent/guardian to discuss the study with other members of the family at home. Contact details for the parent/guardian will be obtained and stored in a sensitization log, to allow field staff to follow potential subjects up, and a further appointment will also be arranged at which recruitment may take place. Informed consent from parents or guardians will be taken prior to any study procedures being undertaken.

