### **Model selection by backwards selection for generalised linear and logistic mixed-effects models**

A multivariable model was first constructed using pneumococcal density (continuous data) as the response variable and including all possible covariates of interest: Group (ref: control vs LAIV), Study timepoint (ref: D0 vs D7 and D21), year of recruitment (ref:2017 vs 2018), presence of asymptomatic respiratory viruses at baseline, age in months, sex, presence of a smoker in the household, type of cooking (re:outdoor open fire vs indoor kitchen). Interactions between group and study timepoint, group and year of recruitment, as well as group and the presence of asymptomatic respiratory viruses were also included.

Backward selection was then undertaken, removing covariates to construct a new model and comparing this reduced model with the previous model using ANOVA-derived P values and Akaike information criteria (AIC). Non-informative covariates were sequentially removed in this way to arrive at the most parsimonious model for our data. Non-significant interaction terms were first removed prior to single covariates. The final model is as stated below:

Pneumococcal density ~ study timepoint + group\*year of recruitment + presence of baseline respiratory viruses + age in months + type of cooking + (1 | participant ID)

A logistic mixed-effects model with pneumococcal carriage (categorical data) as the response variable and including covariates of interest was constructed in a similar way, for each group (LAIV or control) individually. The final model is as stated below:

Presence of pneumococcal carriage ~ study timepoint + presence of baseline respiratory viruses + age in months + type of cooking + (1 | participant ID)

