**Table S7. Viral infections acquired between baseline (day 0) and day 7 in the control group.**

|                                            | 2017
n=48 | 2018
n=42 | P value# |
|--------------------------------------------|----------------------|----------------------|----------------------------|
| Day 7 respiratory viral infections* | 10 (20·8%)    | 17 (40·5%)    | 0·07                |
| Adenovirus                                 | 0 (0·0%)             | 2 (11·8%)            |                            |
| Seasonal coronaviruses (sCoV)              | 1 (10·0%)            | 3 (17·6%)            |                            |
| Parainfluenza 1                            | 0 (0·0%)             | 1 (5·9%)             |                            |
| Influenza B & Rhinovirus                   | 0 (0·0%)             | 2 (11·8%)            |                            |
| Rhinovirus                                 | 8 (80·0%)            | 7 (41·2%)            |                            |
| Rhinovirus & Adenovirus                    | 1 (10·0%)            | 1 (5·9%)             |                            |
| Rhinovirus & sCoV                          | 0 (0·0%)             | 1 (5·9%)             |                            |

\*Shown are new viruses detected at day 7 that were not present at baseline (day 0). Samples where the same virus was detected at day 7 that was present at baseline are not included (n=11). #P value derived from Fisher's exact test comparing the presence of any respiratory virus across years.

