## **11 Potential effects of LAIV on nasopharyngeal microbiota**

The human URT is a dynamic and complex environment, where communities of commensal and potentially pathogenic organisms co-exist. Bacterial and viruses are able to colonise this niche, dependent on interactions with other microbes and host factors. In a steady state, this dynamic process has no adverse consequences for the host and can provide beneficial effects influencing immune function [50], but imbalances can result in pathogenic species outgrowth and subsequent respiratory and invasive disease [51, 52]. Interactions between influenza and bacteria (E.g. *S. pneumoniae* and *S. aureus*) are well documented, resulting in secondary bacterial pneumonia [53, 54]. This is partly explained by an increase in nasopharyngeal bacterial carriage [55] due to epithelial barrier disruption [56, 57], increase in conditions favouring bacterial adhesion [58] and modulation of host innate immunity resulting in increased bacterial load [59-61].

The immediate effects of LAIV on the nasopharyngeal microbiome, however, are less clear. Although an attenuated virus, LAIV infects nasal epithelial cells and parallels some aspects of wild-type influenza host-pathogen interactions. Mouse models show that LAIV induces changes in nasopharyngeal microbiota, temporarily changing pneumococcal and staphylococcal bacterial burden in a similar way to wild-type influenza [62], possibly due to increased type I interferon, known to play a key role in enhanced bacterial colonization [55]. Whereas there are no safety concerns regarding LAIV leading to bacterial pneumonia given the hundreds of thousands of children who have received this vaccine, a temporary increase in bacterial burden could have implications on onward transmission in areas of high pneumococcal colonization, resulting in greater rates of pneumococcal colonization at a population level. Although underpowered, a recent study from a cohort of UK children given LAIV suggested similar observations may be seen in human studies [63]. In a setting like The Gambia where pneumococcal colonisation in children is extremely high [64], this interaction needs to be explored and results used to form the basis for more complex pneumococcal transmission studies if widespread LAIV use is considered.

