## 22 Allocation concealment, randomization and blinding procedures

### 23 Allocation concealment and randomization

Following informed consent, subjects will be assigned a unique subject identification number (section 3.2.2) and details recorded on an enrollment log. If eligibility is confirmed according to the defined inclusion and exclusion criteria (section 5.3), children will be randomized into one of the three equally sized groups as defined in section 3.1 above (for groups A, B and C).

Randomization will be undertaken using pre-prepared, sealed opaque envelopes to maintain allocation concealment. Block randomization stratified by sex will be undertaken using a computer generated randomization sequence pre-prepared by an individual not otherwise involved in the study or its analysis. The block size and randomization sequence will not be known by any member of the investigator team, hence ensuring allocation bias is avoided. Information regarding the group into which a participant has been randomized will be revealed to the team only when opening the envelope.

At the time of randomization, the person undertaking randomization will take the next envelope in numerical sequence. The randomization list will be cross-checked by a second individual both of whom will be required to sign to document the process.

The 35 subjects for group D will be recruited sequentially after recruitment in groups A, B and C have been completed, during the 2nd recruitment season (January – June 2018).

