### **54**    Inclusion criteria

Each subject being initiated on the study protocol must satisfy the following inclusion criteria at study entry:

- Healthy male or female child at least 24 months of age and less than 60 months of age at the time of study entry.
- Resident in the study area and with no plans to travel outside the study area during the period of subject participation.
- Informed consent for the study participation obtained from a parent (or guardian only if neither parent is alive or if guardianship has been legally transferred (see section 11.2).
- Willingness and capacity to comply with the study protocol as judged by a member of the clinical trial team.

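### With no one-child-per-household rule and randomisation by child, a control can live with a vaccinee shedding vaccine virus, which would bias the LAIV-control contrast toward no effect

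*Combined protocol and SAP*

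**What the plan says.** Section 52 (Identification of potential study subjects) gives two recruitment routes. One is community sensitisation, with "parents encouraged to attend with their children to the Health Centre, where recruitment will take place". The other runs through the immunisation clinic: "Older siblings of children attending the Health Centre for their expanded programme of immunization (EPI) schedule will also be recruited".

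Section 54 (Inclusion criteria) admits a "Healthy male or female child at least 24 months of age and less than 60 months of age at the time of study entry". Its only rule about where a child lives is "Resident in the study area and with no plans to travel outside the study area during the period of subject participation". Neither section 55 (Exclusion criteria) nor the eligibility lists at the front of the appendix mention a sibling or household member already in the trial.

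On allocation, section 23 says: "Block randomization stratified by sex will be undertaken using a computer generated randomization sequence pre-prepared by an individual not otherwise involved in the study". Household is neither the unit of allocation nor a stratum. Section 21 sets three groups of 110, two given LAIV and one control, so the ratio is 220:110. The controls are the comparator for the objective on LAIV and the microbiome. They are swabbed on days 0, 7 and 21.

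Section 11 explains why pneumococcal burden is studied: "a temporary increase in bacterial burden could have implications on onward transmission in areas of high pneumococcal colonization". Section 19 lists shedding of vaccine virus by vaccinees on days 2 and 7 as an exploratory endpoint. For control swabs, the footnote to Table 3 states one use, microbiome sequencing.

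The final density model in the appendix has one random term, "1 | participant ID". Section 128 plans a vaccine fixed effect plus random effects for other factors that it does not name.

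**The concern.** Staff following this plan to the letter could enrol two siblings in the same weeks, give LAIV to one and leave the other as a control. The control then shares a home with a child expected to shed vaccine virus. By the reasoning of section 11, that vaccinee may also pass on more pneumococcus.

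If the control acquires the vaccine virus, or extra pneumococcus from the vaccinee, and responds in the same direction as a vaccinated child, density rises in the control group too. The LAIV-control difference then shrinks. A larger sample does not remove such a bias. Section 51 chose recruitment months with little wild-type influenza, to limit interference with the endpoints, but no section deals with vaccine virus reaching the controls.

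**Working it through.** **1. The plan's own power figures.** Section 123 gives at least 90% power for a 2-fold rise with 100 vaccinated children at 80% carriage, and at least 80% power for a 1.5-fold rise with 230 at 90% carriage. Both come from a cited simulation, and no standard deviation is given, so they cannot be reproduced. Solving backwards for a one-sample change in log10 density among carriers (two-sided alpha 0.05, normal approximation):

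- 2-fold: SD = 0.301 × √80 / (1.960 + 1.282) = 0.83.
- 1.5-fold: SD = 0.176 × √207 / (1.960 + 0.842) = 0.90.
- With SD 0.83 the second case has 86% power, so the two statements are compatible.

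Both describe change from baseline in vaccinees. Contamination of controls does not enter them. It affects only the between-group comparison in section 128 and Table S2.

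**2. Chance that a control's co-enrolled sibling is vaccinated.** With 220 LAIV and 110 control children, this is 220/329 = 0.67.

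**3. Dilution of the contrast.** Let f be the share of controls with a sibling enrolled at the same time, and t the chance that a vaccinated sibling's virus reaches the control with the full vaccine effect. Both are assumptions, because the documents give neither.

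- Diluted share: q = f × (220/329) × t.
- Observed difference = true difference × (1 − q) on the log10 scale.
- Power = Φ[(1.960 + z) × (1 − q) − 1.960], with z = 0.842 for 80% and 1.282 for 90%.

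Example for f = 20%, t = 25%: q = 0.20 × 0.669 × 0.25 = 0.033. Then 2.802 × 0.967 − 1.960 = 0.75, which gives 77.3%.

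| f | t | q | 80% power at 1.5-fold becomes | 90% power at 2-fold becomes |
|---|---|---|---|---|
| 10% | 10% | 0.007 | 79.5% | 89.6% |
| 20% | 25% | 0.033 | 77.3% | 88.0% |
| 20% | 50% | 0.067 | 74.4% | 85.7% |
| 40% | 100% | 0.267 | 53.7% | 66.1% |

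The last row is an extreme case, in which a true 1.5-fold effect would appear as 1.35-fold. For scale, Table S2 gives an LAIV coefficient of +0.339 (SE 0.129) for the 2017 reference year. With q = 0.033 the undiluted value would be 0.339 / 0.967 = 0.351, a difference of about 0.012, or 0.09 of a standard error.

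**4. Does a missing household term distort the LAIV-control standard error?** In the difference of means a LAIV child has weight +1/220 and a control −1/110, that is +1 and −2 in units of 1/220. For a sibling pair allocated individually 2:1, both are in LAIV with probability 4/9 (product +1), both are controls with probability 1/9 (product +4), and they are split with probability 4/9 (product −2). The expected product is 4/9 + 4/9 − 8/9 = 0, so the sibling covariance cancels. The variance ratio is 1.00 for 17, 33 or 66 pairs and household ICC 0.1 to 0.5. In 10,000 simulated trials per setting (33 or 66 pairs, ICC 0.3 or 0.5), type I error without a household term was 4.8% to 5.0%.

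**The case against.** The strongest reply is that the point rests on silence. The immunisation-clinic route uses the attending infant to find an older brother or sister. It does not say that two siblings will both be enrolled, and no document counts shared households. Exposure also needs overlap in time: section 51 expects about 7 to 8 children per week over two six-month seasons, and a control is followed for 21 days. Every input for the size is assumed, and modest values cost little power. All of this stands, and it limits the weight of the point. It does not remove it, because nothing in the plan prevents a shared household or would show how many there are.

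A reader might also infer that siblings treated as independent make the standard error of the LAIV effect too small, and that a household random intercept is needed. The documents do not support this. The usual design effect, 1 + (m − 1) × ICC, is for allocation by cluster. Here allocation is by child, and step 4 shows that the omission is neutral for this contrast. A household intercept would not remove spillover either. Clustering could matter only for comparisons that randomisation does not protect, such as IgA responders against non-responders. There the variance could rise by about 1% to 20% (1 + f × ICC, taking f here as the share of children with a co-enrolled sibling, 0.1 to 0.4, and ICC 0.1 to 0.5). Section 128 also leaves room for further random effects.

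Table S7 invites another inference. It lists two 2018 controls under "Influenza B & Rhinovirus" as new at day 7, and the vaccine contains a B strain. The table does not separate vaccine from wild-type virus and gives no household links, so it neither shows nor excludes spillover.

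**Conclusion.** The gap is real: recruitment through families, no household limit and allocation by child together allow a control to live with a concurrently enrolled vaccinee. Any spillover would pull the LAIV-control contrast for primary objective (iii) toward no effect, provided that the response in an exposed control has the same sign as the direct effect.

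The size cannot be determined from the documents. With f up to 20% and t up to 25%, the loss is under 3 power points. It becomes serious only if many controls have a vaccinated sibling and transmission is common. The documents do not support reading this as a flaw that invalidates the comparison, as an error in the stated power, or as evidence that spillover took place. It is a cheap improvement to the design, with a check worth running.

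**What to change.** Add an entry criterion of one child per household. The cost is one eligibility line and a few eligible siblings not enrolled.

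The appendix already reports results for both recruitment seasons, so for children already enrolled only a check is possible:

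- Identify shared households as far as records allow, and report their number. Section 52 provides for logging parents' contact details, and the appendix uses household covariates (a smoker in the home, type of cooking), so linkage looks feasible. The documents do not show that a household identifier was collected.
- If any are found, repeat the LAIV-control density and microbiome comparisons without controls who live with an LAIV recipient enrolled at an overlapping time.

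If no siblings were enrolled together, one sentence saying so closes the point. No household random intercept is needed for the LAIV-control contrast.
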